## Abstract

**Background:**

Breastmilk is the ideal nutrition for preterm infants. Yet, breastmilk feeding rates among preterm infants are substantially lower than those of full-term infants. Barriers incurred through hospital care practices as well as the physical environment of the neonatal intensive care unit (NICU) can result in physical and emotional separation of infants from their parents, posing a substantial risk to establishing and maintaining breastfeeding. Additionally, current practitioner-focused care provision in the NICU can result in decreased breastfeeding self-efficacy (BSE), which is predictive of breastfeeding rates in mothers of preterm infants at 6 weeks postpartum.

**Methods:**

Family Integrated Care (FICare) integrates and supports parents to actively participate in the care of their infant while in the NICU. Nested within the broader FICare trial, we will conduct an explanatory sequential mixed methods study to investigate if FICare improves maternal BSE and rates of breastmilk feeding in moderate and late preterm infants at discharge from the NICU. In phase 1, we will calculate the mean difference between admission and discharge BSE scores for the intervention group. Mothers who score in the top and bottom 20th percentile of change scores will be invited to participate in a semi-structured telephone interview exploring maternal experiences with infant feeding in the NICU. We will conduct inductive thematic analysis to identify and describe the facilitators and barriers of FICare on maternal feeding experiences. Once data saturation is achieved and themes have been established, phase 2 will revisit the quantitative data to determine whether FICare was impactful on BSE and breastmilk feeding rates. Findings from the qualitative and quantitative phases will be integrated to determine how infant feeding experiences on FICare units work to improve or detract from maternal BSE and rates of breastmilk feeding.

**Discussion:**

FICare may help to improve maternal BSE and rates of breastmilk feeding in moderate and late preterm infants. Improved breastmilk feeding outcomes can have a substantial impact on overall infant health, developmental outcomes, and maternal-infant bonding and will help to improve long-term health outcomes for moderate and late preterm infants.

**Trial registration:**

(NCT02879799). Registered May 27, 2016 protocol version June 9, 2016 Version 2.

**Electronic supplementary material:**

The online version of this article (10.1186/s13006-018-0168-7) contains supplementary material, which is available to authorized users.

## Background

Globally, preterm birth rates (born prior to 37 weeks gestational age [GA]) range from 5 to 18% [1, 2]. Over 80% of preterm infants are born moderate (32 weeks and zero days [32^0/7^] to 33^6/7^ weeks GA) or late (34^0/7^ weeks to 36^6/7^ weeks GA) preterm [3, 4]. Prematurity is a significant contributor to child morbidity and a primary concern for child health clinicians [1, 2, 4, 5]. Although not as medically complex as their early preterm (born prior to 32 weeks GA) counterparts, moderate and late preterm infants are at risk for several health and developmental issues [6], and often require level II neonatal intensive care [7]. Appropriate nutrition beginning at birth is a key component to lifelong health [8] and breastmilk feeding is the recommended optimum feeding method for preterm infants [9–12]. However, breastmilk feeding rates among preterm infants are substantially lower than those of full-term infants [13, 14]. Moderate and late preterm infants may have poor feeding skills that limit breastmilk intake and jeopardize infant growth and development [6]. The physical environment of the neonatal intensive care unit (NICU), and practices that physically and emotionally separate infants from their mothers, pose a risk to establishing and maintaining breastmilk feeding [15]. Despite recommendations for family centered care [16–18], the traditional model of care in NICUs situates healthcare professionals as the primary care provider. Frequently, mothers are relegated to the role of supplementary care provider or observer [18], which may limit time spent with their infant(s) and educational opportunities [19]. The traditional model of care can result in feelings of parental detachment, ineffective parenting, parenting stress, and loss of control [19, 20]. Further, traditional models of care decrease parenting and breastfeeding self-efficacy, potentially contributing to lower breastmilk feeding rates [15]. Integrating mothers into the care of their infants in the NICU may improve maternal breastfeeding self-efficacy and increase rates of breastmilk feeding at discharge.

### Breastfeeding self-efficacy

Breastfeeding self-efficacy is a social cognitive theory adapted by Dennis [21]. Breastfeeding self-efficacy captures how a mother perceives her ability to breastfeed rather than her *actual* ability to succeed at breastfeeding [21–23]. Mothers with high self-efficacy are often able to overcome barriers that those with low self-efficacy would find overwhelming [24]. Breastfeeding self-efficacy is informed by four sources of information: (i) performance accomplishments, (ii) vicarious experience of seeing other mothers breastfeed, (iii) verbal persuasion by influential others, and (iv) the mother’s physiological/affective state [21, 25]. Breastfeeding self-efficacy can predict breastfeeding outcomes at 1 and 2 months postpartum in mothers of full-term infants [26] and it is a modifiable factor that can influence breastfeeding success [20, 26–28]. Few studies have been conducted using breastfeeding self-efficacy theory in mothers of preterm infants [20, 29]. Interventions to improve breastfeeding self-efficacy may improve breastmilk feeding rates and subsequent health outcomes for moderate and late preterm infants.

### Study aim

This study is nested within a larger cluster randomized control trial (cRCT) assessing multiple outcomes of a Family Integrated Care (FICare) for moderate and late preterm infants in level II NICUs [30]. The primary outcome of the FICare cRCT is to evaluate the effect of FICare on length of stay in the level II NICU. The aim of the *present* study is to determine if FICare improves maternal breastfeeding self-efficacy and resultant breastmilk feeding rates in mothers of moderate and late preterm infants who were admitted to a level II NICU. The specific objectives are:i.To determine if FICare is effective in improving breastfeeding self-efficacy in mothers of moderate and late preterm infants between admission to and discharge from a level II NICU.ii.To determine if FICare is effective in increasing breastmilk feeding rates in mothers of moderate and late preterm infants at discharge from the NICU.iii.To explore maternal experiences with infant feeding while admitted to the NICU.iv.To determine if or how maternal experiences with infant feeding work to inform maternal breastmilk feeding rates while in the FICare NICU environment.

## Methods

We will conduct an explanatory, sequential mixed methods study (Fig. 1). Nested within the larger FICare cRCT, we will examine the breastfeeding self-efficacy scores of participants in the intervention arm of the study. Using maximum variation sampling, we will select a sub-sample of mothers demonstrating the highest and lowest breastfeeding self-efficacy change scores during their infants’ hospital stay. We will conduct a semi-structured telephone interview to explore maternal experiences of infant feeding during hospitalization. We will then use these experiences to explain how, or if, FICare informs maternal breastfeeding self-efficacy and resultant breastmilk feeding rates in mothers of moderate and late preterm infants. We adhered to the Standard Protocol Items: Recommendations for Interventional Trials (SPIRIT) guidelines in the design of the protocol (Additional file 1) [31].

**Fig. 1 Fig1:**
[figure not shown]
Study flow diagram. Overview of the study design. Rectangles depict quantitative phase, ovals depict qualitative phases, and hexagons depict integration phases. Abbreviations: cluster randomized control trial (cRCT), Breastfeeding Self-efficacy Scale (BSES), covariates (Cov), length of stay (LOS), Edinburgh Postnatal Depression Scale (EPDS)

### Rationale for mixed methods design

There is a call to develop breastfeeding research methodologies that embrace “interpretation from the social sciences” rather than strictly relying on quantitative measures of breastmilk feeding rates [32]. Unilaterally implementing one of the two dominant research paradigms will not fully honour the complexity of breastfeeding self-efficacy and breastmilk feeding within the NICU [33]. Utilizing quantitative methodologies to measure breastfeeding self-efficacy and breastmilk feeding rates and qualitative methodologies to explore infant feeding experiences will allow for our research objective to be explored from multiple perspectives [33]. By exploring maternal experiences associated with feeding moderate and late preterm infants while in the NICU, we can better understand if FICare is a successful model of care to improve maternal breastfeeding self-efficacy and breastmilk feeding rates. Semi-structured interviews will allow for intimate insights from mothers to emerge that will provide substantive content as well as individual experiential data [34, 35]. Further, examining both the quantitative and qualitative components of breastfeeding self-efficacy will provide an enhanced understanding of breastfeeding self-efficacy results and resultant infant feeding outcomes.

### FICare cluster randomized controlled trial

All level II NICUs in the province of Alberta, Canada (*N* = 10) will be randomized into a standard care control group (*n* = 5) or an intervention group (*n* = 5). Each intervention site will have specially trained registered nurse super-users who are responsible to recruit participants, deliver the intervention, and collect data. To ensure intervention fidelity, we will conduct site visits four times per year to assess adherence and compliance with the intervention components. We will also monitor for activities (e.g. policy changes, guidelines, unit practices) that may influence implementation of FICare.

#### FICare model

FICare is a model of care that actively supports families to participate in the care of their infant and was originally introduced to Canada at the Mount Sinai Hospital level III NICU in Toronto, Ontario [36]. The intervention originated from the Humane Neonatal Care model developed in Tallinn, Estonia, where parents actively participated in the care of their infants, while nurses and psychologists provided education and support [36]. Existing research regarding the effectiveness of FICare is limited to level III NICUs. A recent cRCT examining the impact of FICare in level III NICUs found that infants exposed to the FICare intervention were significantly more likely to be exclusively breastmilk feeding at discharge (279 [70%] of 396) compared to those receiving standard care (394 [63%] of 624; *p* = 0.016) [37]. As such, it is important to determine if the FICare model is similarly effective for improving breastmilk feeding outcomes in moderate and late preterm infants admitted to a level II NICU.

#### FICare intervention

Families participating in the FICare study will be required to spend a minimum of six hours per day, or approximately three feeding times, at the NICU. Nurses will support and educate mothers and fathers in their parenting role with a focus on actively involving them in the care of their infants while in the NICU. Parents will share in the care of their infant(s) as soon as they are able, starting with simple tasks, such as skin-to-skin contact and diapering, and progressing to more complex tasks, such as feeding. FICare involves three main components (Fig. 2): (i) information sharing, (ii) parent education (including parent-education pathways and specially designed apps), and (iii) parent support. Information sharing is bidirectional and involves parents verbally reporting on their infants’ progress at daily bedside multidisciplinary rounds and actively contributing to discussions about the plan of care. Parent support will involve one-on-one discussions with veteran parents. Veteran parents (those who have previously had an infant in the level II NICU environment) will provide practical advice, guidance, and support to parents in the FICare study. Finally, parent education will include standardized, evidence informed parent education delivered individually or in group settings.

**Fig. 2 Fig2:**
[figure not shown]
FICare model of change

#### FICare context – Level II NICUs

In Alberta, infants admitted to a level II NICU are generally born after 32 weeks, weighing more than 1500 g. Nutritionally, these infants tend to be on total parenteral nutrition, receiving gavage feeds, or full oral feeds, depending on their developmental maturity [7]. All 10 level II NICUs in Alberta formally support the provision of mother’s own milk as the first choice for infant feeding [38]. While there is no formalized breastfeeding education requirement [39] for practitioners working in NICUs, all mothers have access to International Board Certified Lactation Consultants. Visitation models vary among the 10 sites, with most NICUs allowing parents unrestricted 24-h access to their infant. There is a mix of open and closed ward models, with five of the NICUs planning to transition to single room wards during the timeline of the FICare study.

#### FICare cRCT inclusion criteria

The FICare cRCT will include mothers of preterm infants born between 32^0/7^ and 34^6/7^ weeks GA, admitted to a level II NICU in Alberta, who speak, read, and write English. To ensure an adequate dose of the intervention, infants must have a minimum NICU stay of 5 days. Infants born greater than 35 weeks GA were excluded from the study as they would not meet the minimum 5-day requirement if discharged around 36 weeks GA. We will exclude mothers of infants with social risk that may interfere with their ability to engage in FICare, and infants with a severe congenital abnormality or chromosomal anomaly, or receiving palliative care.

#### FICare sample size

We based sample size estimates on the primary outcome, length of stay. Due to an anticipated skewed distribution for length of stay, we used a natural logarithm transformation to calculate sample size [40]. To achieve a power of 0.80, we need to recruit 181 mothers into each group for the primary outcome of length of stay; and 211 to achieve a power of 0.9. In 2014, there were 1030 moderate and late preterm infants admitted to a level II NICU in Alberta. To account for a response rate of 80% [36], attrition, and infants with a length of stay of ≤5 days (6.08%), we will approach 824 potential participants over the 30-month recruitment period. This will also ensure that the sample size, 330 per group, is sufficient to assess secondary outcomes and to provide the qualitative sample for the study.

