#### Data analysis

Statistical analysis of the quantitative results will be performed using Stata Data Analysis and Statistical Software. The primary outcome of the statistical analysis is to determine if a difference exists in: i) breastfeeding self-efficacy scores (BSES-SF) and ii) breastmilk feeding rates, between the control and intervention groups. Results from the BSES-SF will be treated as continuous data whereas results from breastmilk feeding rates will be treated as categorical data [20, 43]. Characteristics of participants and scores on scales will be presented as descriptive statistics (means, frequencies, and percentages). We will use an omnibus test (Hotelling’s t-tests and Chi square) to assess for baseline differences between intervention and control groups on socio-demographic and health characteristics, breastfeeding self-efficacy, and breastmilk feeding rates.

To test if there is a difference in breastfeeding self-efficacy and breastmilk feeding rates between the intervention and control groups, we will use Hierarchical Linear Modeling (HLM; also known as multilevel modeling or mixed-effect modeling) and Hierarchical General Linear Modeling (HLGM), respectively. This study is nested in a larger cRCT and there is a potential for variance in care delivery at each of the NICU sites. As such, there are multiple levels of data that need to be considered to accurately assess the effectiveness of the intervention on breastfeeding self-efficacy and breastmilk feeding rates. By simultaneously investigating the relationships between the different levels of data, HLM and HGLM analysis can account for variance among variables at different levels [44]. The HLM approach will allow for the two observations (admission and discharge from the NICU) by treating each participant’s breastfeeding self-efficacy score and breastmilk feeding rate at each assessment point as single data points [44]. There will be two levels of analysis in the data: Level 1 will refer to the outcome variables of breastfeeding self-efficacy and breastmilk feeding rates; while Level 2 will be the maternal or subject effect. We will enter the subject effect into the model as a random effect to capture within and between-subject variation [44]. The group effect of intervention/control will be entered as fixed effect to determine if the intervention is effective.

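### The powers of 0.80 (181 mothers per group) and 0.90 (211) name no allowance for randomising 10 NICUs, and as a pair they fit no 5 v 5 cluster calculation; power should be restated for the design as randomised

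*Protocol article*

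**What the plan says.** The section on the FICare cluster randomized controlled trial makes the NICU the unit of randomisation. All 10 level II units in Alberta "will be randomized into a standard care control group" or an intervention group, five to each.

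The FICare sample size section counts in mothers: "To achieve a power of 0.80, we need to recruit 181 mothers into each group for the primary outcome of length of stay". For a power of 0.90 its figure is 211 per group. The one thing it says about how these figures were reached is that "we used a natural logarithm transformation to calculate sample size [40". It gives no effect size, SD, significance level, ICC, cluster size or design effect.

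It then turns to recruitment: "we will approach 824 potential participants over the 30-month recruitment period". The reasons given are an 80% response rate, attrition and short stays (6.08%). The planned sample is 330 per group, which the section also calls sufficient for the secondary outcomes.

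The Data analysis section of the quantitative phase accepts that "there is a potential for variance in care delivery at each of the NICU sites". The section on the level II context describes differing visitation and ward models, with five units planning to move to single rooms during the study.

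**The concern.** When 10 units are randomised, what is known about the arm comparison is limited by the number of units as well as the number of mothers. Mothers in one NICU share staff, discharge practice and ward layout, so their infants' lengths of stay are likely to be correlated. A power stated for a number of mothers per group, without reference to the NICUs, reads as the power of an individually randomised trial of that size.

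The article gives its own grounds for expecting differences between sites. If the figures carry no clustering allowance, a null result on length of stay would be read as coming from a trial with 80–90% power when the true power could be lower. Within Alberta the shortfall could not be met by adding units, because all 10 are already in the trial.

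**Working it through.** **Inputs from the Protocol article.** 181 per group for 0.80; 211 per group for 0.90; 330 per group planned; 5 NICUs per arm.

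**Assumptions, since the article gives none of these.** Two-sided 5%; NICUs of equal size; ICC between 0.005 and 0.02. All 330 per group are taken as analysed. This is generous, since 824 × 0.80 / 2 = 329.6 uses up only the response rate.

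**Reproducing the stated figures.** Neither 181 nor 211 can be rebuilt, because the effect size and SD are not stated. The pair can be checked against itself.

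**Step 1: do 181 and 211 fit together in a 5 v 5 design?** With n mothers per arm in 5 NICUs:

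- design effect DE = 1 + (n/5 − 1) × ICC
- non-centrality = d × √(n / (2 × DE))
- power ≈ Φ(non-centrality − 1.960)

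Moving from 0.80 to 0.90 for a fixed effect d requires the squared non-centrality to rise by ((1.960 + 1.282) / (1.960 + 0.842))² = 1.339. Moving from 181 to 211 raises it by (211/181) × (DE at 181 / DE at 211).

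- ICC 0: 211/181 = 1.166. Non-centrality 2.802 × √1.166 = 3.025, power 0.857.
- ICC 0.01: 1.166 × 1.352/1.412 = 1.116. Non-centrality 2.802 × √1.116 = 2.960, power 0.841.

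The gain shrinks as the ICC rises, so 0.857 is the ceiling. If 181 gives 0.80, then 0.90 needs about 243 per group at ICC 0, 258 at 0.005 and 277 at 0.01. An 8-df t test gives nearly the same (211 gives 0.856 at ICC 0 and 0.841 at 0.01).

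**Step 2: power if 181 is unclustered.** The implied effect is d = (1.960 + 0.842) × √(2/181) = 0.294 SD of log length of stay. This is back-solved; the sponsor does not state it. Power on that effect:

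| ICC | DE, 181 | Power, 181 (normal) | DE, 330 | Power, 330 (normal) | Power, 330 (t, 8 df) |
|---|---|---|---|---|---|
| 0.005 | 1.18 | 0.73 | 1.33 | 0.91 | 0.82 |
| 0.01 | 1.35 | 0.67 | 1.65 | 0.84 | 0.73 |
| 0.02 | 1.70 | 0.57 | 2.30 | 0.70 | 0.59 |

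Example, 330 per group at ICC 0.01: DE = 1 + (66 − 1) × 0.01 = 1.65; non-centrality = 0.2945 × √(330 / 3.30) = 2.945; power = Φ(0.985) = 0.84.

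**Step 3: largest ICC at which 330 per group keeps 0.80.** Normal approximation: (330/181 − 1) / (66 − 1) = 0.0127. With the 8-df t test, solved numerically: 0.006.

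**Step 4: limit set by five NICUs per arm.** With unlimited mothers, 0.80 on this effect needs ICC < 5/181 = 0.028 (normal approximation).

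**The case against.** The strongest reply is that silence is not omission. The figures belong to the parent trial's primary outcome, and the article refers elsewhere for that trial and for the calculation method. Every input is missing, not only the ICC, which is ordinary condensation in an article. The listed allowances explain why 824 mothers are approached; they do not say how 181 and 211 were derived, so a design effect inside those figures would not appear there. All of this stands, and a missing ICC alone would not be a finding.

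It does not rescue the printed pair. A built-in design effect widens the gap required between the two sample sizes when the number of NICUs is fixed, and the printed gap is already too narrow with no clustering. Equally, the pair does not fit the individual formula (243 needed against 211), so the mismatch does not prove that clustering was ignored.

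A second reply is that 330 per group are planned, not 181. That also stands: 330 is 1.82 times 181 and holds 0.80 at small ICCs. The section attributes the larger recruitment to other causes, however, and the margin is gone at an ICC of about 0.013 or less.

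A third is that the article does not describe the length-of-stay analysis, so an 8-df test is an assumption. It is, and the normal-approximation results are therefore given beside it.

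**Conclusion.** The point holds in a conditional form. For a common effect at two-sided 5%, 181 and 211 cannot both be right for a 5 v 5 cluster design at any ICC. If 181 gives 0.80, 211 gives no more than 0.857.

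If the figures are also unclustered, 181 per group falls to 0.57–0.73 for ICCs of 0.02 down to 0.005. The planned 330 per group lies between 0.70 and 0.91 (normal) or 0.59 and 0.82 (8-df t) over the same range. These powers rest on the assumed ICCs, equal NICU sizes and an effect back-solved from 181. Unequal NICUs would lower them further.

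A reader might infer more: that clustering was certainly ignored, or that the trial as planned has only about 50–65% power. The article supports neither. It does not show how 181 and 211 were obtained, it gives no ICC, and powers that low come mainly from 181 per arm rather than the 330 planned. Nor does it claim a specific power for breastfeeding self-efficacy or breastmilk feeding, so the figures above should not be carried over to those outcomes.

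**What to change.** In the FICare sample size section, replace the unqualified 181 for 0.80 and 211 for 0.90 with the power, or the difference detectable at 0.80, for the design as randomised: 330 mothers per group in 5 NICUs per arm (about 66 per NICU if equal). Calculate it from the sponsor's own effect size and SD for log length of stay, over a stated ICC range, with a small-sample reference distribution that reflects 10 clusters. If 181 and 211 already contain a design effect, state the ICC and cluster size used and correct whichever figure does not follow. Do not insert 0.294 SD as the sized effect; it is an inference from 181, not a figure of the sponsor's.

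The cost is one recalculation and a reworded paragraph. The stated power may become less favourable. No mothers, sites or procedures are added.

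### 330 per group is called sufficient for secondary outcomes, but gives only about 50% power at best for the one feeding effect cited, and its allowance for losses does not follow from the stated figures

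*Protocol article*

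**What the plan says.** Under FICare sample size, the article says: "We based sample size estimates on the primary outcome, length of stay". The result is 181 mothers per group for 80% power and 211 for 90%. It then turns to expected losses. Besides an 80% response rate it lists "attrition, and infants with a length of stay of ≤5 days (6.08%), we will approach 824 potential participants". The next sentence draws the conclusion at issue: "This will also ensure that the sample size, 330 per group, is sufficient to assess secondary outcomes".

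Under FICare model, the article reports exclusive breastmilk feeding at discharge in the level III trial as "279 [70%] of 396) compared to those receiving standard care (394 [63%] of 624", and adds that "it is important to determine if the FICare model is similarly effective for improving breastmilk feeding outcomes" in level II units.

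Length of stay is the parent trial's primary outcome. The two outcomes of this nested study, BSES-SF and breastmilk feeding (Table 1), are therefore both secondary outcomes of the parent. The sentence on 330 per group is the only justification of size that the article gives for them.

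**The concern.** Sufficiency for secondary outcomes is stated as a property of the design, although only length of stay was sized. The article gives no effect size, significance level, ICC or power for feeding or BSES-SF. It does give one feeding result that it hopes to see repeated, so the claim can be tested against that. Separately, the step from 824 approached to 330 per group appears to use up the whole allowance on non-response, although the text says that attrition and short stays are also covered.

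What is at stake is the reading of a null result. A reader told that the sample was sufficient may take a non-significant feeding comparison as evidence that FICare does not help in level II units. For an effect of the cited size, such a result is about as likely as not without clustering, and more likely than not with it.

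**Working it through.** **Inputs from the article.** 824 approached; 80% response; stays of ≤5 days 6.08%; attrition named without a figure; 330 per group; 10 NICUs, 5 per arm; 279/396 v 394/624 (printed as 70% v 63%); 181 and 211 per group for length of stay; 1030 admissions in 2014.

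**Assumptions.** Two-sided 0.05, since neither level nor sidedness is stated. ICC from 0 to 0.05, since none is stated. Equal NICU sizes, m = 330/5 = 66.

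**1. Reproducing 330.** 824 × 0.80 = 659.2, and 659.2 / 2 = 329.6. The stated figure is obtained from the response rate alone. Taking off short stays gives 329.6 × (1 − 0.0608) = 309.6, about 310 per group. With a further 10% attrition (my assumption), 309.6 × 0.90 = 278.6, about 279. To keep 330 per group net of short stays alone, 660 / (0.80 × 0.9392) = 878.4, so 879 would have to be approached.

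**2. Power for the cited feeding effect, no clustering.** Power = Φ[(|p1 − p2| − 1.96·SE0) / SE1], with SE0 = √(2p̄(1 − p̄)/n), SE1 = √([p1(1 − p1) + p2(1 − p2)]/n) and n = 330.

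- Rounded rates, 0.70 v 0.63: SE0 = 0.03674 and SE1 = 0.03664, so (0.0700 − 0.0720)/0.03664 = −0.055 and power is 47.8%. Unpooled and arcsine versions give 48.0% and 47.9%.
- Raw counts, 0.7045 v 0.6314: SE0 = 0.03666 and SE1 = 0.03655, so (0.0731 − 0.0719)/0.03655 = 0.035 and power is 51.4%.
- One-sided 0.05: 60% with rounded rates, 64% with raw counts.
- At 310 per group, two-sided: 45.5% and 48.9%.
- Number per group for 80% power, two-sided: 713 with rounded rates, 650 with raw counts.

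**3. With clustering.** The design effect is 1 + (66 − 1) × ICC and the effective n is 330 / design effect (two-sided, normal approximation).

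| ICC (assumed) | Design effect | Effective n per group | Power, rounded rates | Power, raw counts |
|---|---|---|---|---|
| 0 | 1.00 | 330 | 48% | 51% |
| 0.005 | 1.325 | 249 | 38% | 41% |
| 0.01 | 1.65 | 200 | 32% | 34% |
| 0.02 | 2.30 | 143 | 24% | 26% |
| 0.05 | 4.25 | 78 | 15% | 16% |

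**4. Detectable differences, 80% power, 330 per group.** Normal approximation throughout. The feeding difference is upward from 63%. The BSES-SF difference, without baseline adjustment, is (1.960 + 0.842) × √(2 × design effect / 330).

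| ICC (assumed) | Feeding, points | BSES-SF, SD |
|---|---|---|
| 0 | 10 | 0.22 |
| 0.01 | 13 | 0.28 |
| 0.05 | 20 | 0.45 |

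Using t on 8 degrees of freedom (10 NICUs minus 2) makes these somewhat larger; for BSES-SF at ICC 0.01 and 0.05 they become 0.32 and 0.51 SD.

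**5. Another derivation of 824.** 1030 × 0.80 = 824 exactly. If 824 already contains the response rate, then 660/824 = 0.80 is a second allowance of 20%. After short stays, 824 × 0.9392 = 773.9, and 660/773.9 = 0.853, which leaves room for about 15% attrition.

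**The case against.** Four objections have force.

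First, 70% v 63% is not a design target. It is a background result on exclusive feeding in level III units. The planned feeding outcome has several categories and is modelled with admission and discharge measurements, so a two-proportion test is only a stand-in. This stands. It limits the conclusion to that effect, judged by a simple comparison.

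Second, a reader might infer that power is below 50% whatever is assumed. The article's own counts give 51% without clustering, and a one-sided test gives 60% to 64%. What holds is that no variant tried reaches 80%.

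Third, a reader might infer that the sample is too small for every secondary outcome, BSES-SF included. The article states no target for BSES-SF, and 330 per group detects about 0.22 SD before clustering. The number completing the scale will be lower, because mothers who have weaned or do not plan to breastfeed are not given it, but by how much is not stated. Power details for secondary outcomes may also lie in the parent protocol, which is not shown. Their absence from the article is no fault; the fault is the unqualified statement of sufficiency.

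Fourth, a reader might infer that 330 is certainly not net of losses. The 1030 × 0.80 derivation fits the numbers too, and would make 330 a net figure. Against it, the text says "we will approach 824 potential participants over the 30-month recruitment period", whereas on that derivation 824 would be those who agreed. It would also set a single year's admissions against a 30-month period. The reading in which losses are uncovered is therefore probable, not certain.

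**Conclusion.** The statement that 330 per group is sufficient for secondary outcomes is wrong for the one feeding effect the article cites, and unsupported for the others. For that effect, power is about 50% at best with a two-sided 0.05 test and no clustering. It is about 32% to 34% at an ICC of 0.01 and 15% to 16% at 0.05. The significance level, sidedness and ICCs are assumptions; the rates, the 330 and the five NICUs per arm are the article's own.

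As written, 330 leaves no room for short stays or attrition. The analysable number would be about 310 per group less an attrition that is not stated, unless 824 was derived from 1030.

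It does not follow that the parent trial is undersized for its primary outcome. On the stated numbers, about 310 per group exceeds both 181 and 211.

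**What to change.** - Remove the claim of sufficiency for secondary outcomes, or limit it to the differences that can be detected.
- State how 824 was obtained, and whether 330 is the number enrolled or the number analysable. If 824 is the number approached, give the analysable number as about 310 per group less attrition, and state the attrition assumed.
- Report detectable feeding and BSES-SF differences for 10 NICUs over a stated ICC range, by one method throughout. The second table in the working can serve, recomputed for the analysable number and, for BSES-SF, for the mothers expected to complete the scale.
- State that a non-significant feeding result would not rule out a 7-point difference.

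No extra recruitment or design change is involved. The only cost is that the stated figures look less favourable.
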